## Treatment period (week 0-24)

Patients will be hospitalized the evening or the morning before study drug administration and will be discharged from the hospital 24 hours after dosing.

During hospitalization, patients will undergo a series of assessments (see schedule of assessments, section 6.5). The last available values measured prior to first study drug administration will be considered baseline measurements against which measurements during the treatment period will be compared.

Patients are to refrain from exercise other than the normal daily activities for 24 hours after injection of study medication.

On dosing days study drug administration will take place in the morning upon completion of all necessary pre-dose assessments. The following assessments will be performed: vital signs, ECG, safety biochemistry and haematology, urinalysis and biomarkers. In addition, blood sampling for PK will be performed on the first dosing day. Twenty-four hours after the study drug administration, AEs will be assessed and the patient will be discharged if in good general health. Hereafter the patients will leave the unit.

Patients will return to the hospital for ambulatory visits or hospitalization for the treatment administration visits according to the schedule of assessments, section 6.5.

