| **Statistical methods**  **Statistical analysis methods**  The primary analysis will be done on the treatment period, i.e. once all patients completed the 24 week timepoint. An additional analysis will be performed at week 48.  Safety population  The safety population will comprise of all patients who received at least one dose of treatment.  Full analysis population (FAS)  The full analysis set (FAS) consists of all patients who received at least one dose of treatment and in whom at least one effect assessment is available beyond baseline.  Sample size  Since this is the first study in patients with MS the sample size is based on medical and practical grounds rather than statistical grounds.  Safety parameters  No formal statistics will be employed   - Adverse events (AEs) will be coded and presented using MedDRA. The overall incidence, the incidence of related as well as the incidence of serious adverse events (SAEs) will be summarized per dose and by body system in tables. - Local tolerability will be presented by overall incidence by treatment group per symptom. - Vital signs (supine blood pressure and heart rate) and body temperature: Descriptive statistics (n, mean, standard deviation, median, minimum, and maximum) will be provided for blood pressure, heart rate and body temperature and for changes from baseline. - Hematology, biochemistry and urinalysis parameters: Descriptive statistics (n, mean, standard deviation, median, minimum, and maximum) will be provided on values at baseline and all post-dose assessments. Descriptive statistics will be calculated on the change from baseline values. Out-of-normal-range values will be indicated for each parameter. The change in out-of-normal-range values after administration and at follow up versus baseline will be summarized per group by means of shift-tables. - ECG: Descriptive statistics (frequency, mean, standard deviation, median, minimum, and maximum) on ECG parameters will be provided at baseline and at all post-baseline assessments. Changes from baseline values will be calculated and descriptive statistics will be computed. Shift tables will also be provided to indicate changes in ECG parameters over time.   PK parameters  Descriptive statistics (n, mean, standard deviation, median, minimum, and maximum, plus Geometric mean and CV for C_max_ and AUC and the derived parameters) will be provided for the PK parameters.  Evaluations of dose-proportionality and effects of multiple dosing will be performed.  Effect parameters  Descriptive statistics (n, mean, standard deviation, median, minimum, and maximum) at each visit will be provided for all effect parameters and as well as change from baseline (n, mean, standard deviation, median, minimum, and maximum).  A Student’s T-test will be performed to analyze the changes in the absolute percentage of proliferated T-cells and of the cell division index over time.  Details on the analysis methods to be used for other effect parameters will be specified in the statistical analysis plan. | |

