# Treatments

## Treatments administered

The pharmacy or an unblinded nurse not involved in clinical conduct of the study will prepare all study medication for all patients according to the treatment randomization list.

Patients will receive a single dose of study medication as intravenous bolus injection administered in the arm every two months, for a total of three times during the study. The required amount of study medication will be administered over 30 seconds to the patient via an intravenous catheter.

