## Follow-up period (week 24-week 48)

During the follow-up period, patients will return to the hospital for ambulatory visits twice to undergo the assessments according to the schedule of assessments, section 6.5.

The last available values measured prior to first study drug administration will be considered baseline measurements against which measurements during the follow-up period will be compared.

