^7^ On dosing days blood pressure, pulse rate and temperature will be measured before and 1 hour after dosing; respiration rate only pre-dose.

All assessments are to be done prior to study drug administration unless otherwise stated.

^8^ Ten patients only; one sample collected to further investigate the stability of blood samples

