### Vital Signs

Blood pressure (systolic (SBP) and diastolic (DBP)), pulse rate and respiration rate after 10 minutes supine rest will be recorded on each dosing days and at weeks 36 and 48. On dosing days, evaluations will be done pre-dose and, in addition, blood pressure and pulse rate will be assessed at 1 hour after dosing. Automatic or manual devices may be used. All devices must have been calibrated in the previous 12 months. Calibration certificates must be available on request.

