### Body temperature

Body temperature will be measured at each dosing visit. On dosing days, body temperature will be measured pre-dose and at 1 hour after dosing.

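### The planned change from the day-0 baseline does not isolate the acute change in blood pressure, pulse and temperature after doses 2 and 3; a same-visit contrast should be added

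*Protocol*

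**What the plan says.** Protocol section 6.2 (Treatment period) fixes the comparator in these words: "last available values measured prior to first study drug administration will be considered baseline measurements against which measurements during the treatment period". Section 6.3 carries the same reference into follow-up: the values before the first dose "will be considered baseline measurements against which measurements during the follow-up period will be compared".

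Dosing takes place "every two months, for a total of three times during the study" (section 5.1); Table 6-1 places the doses at day 0, week 8 and week 16. Footnote 7 of that table reads: "On dosing days blood pressure, pulse rate and temperature will be measured before and 1 hour after dosing; respiration rate only pre-dose". Section 7.2.4 agrees for blood pressure and pulse ("evaluations will be done pre-dose and, in addition, blood pressure and pulse rate will be assessed at 1 hour after dosing"), and section 7.2.5 agrees for temperature ("body temperature will be measured pre-dose and at 1 hour after dosing").

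For the analysis, the synopsis says that descriptive statistics "will be provided for blood pressure, heart rate and body temperature and for changes from baseline". Section 10.3.2 adds individual and summary presentation of these variables, descriptive only. No section defines a change from the pre-dose value of the same visit.

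**The concern.** At day 0 the fixed baseline is normally that morning's pre-dose value, so the 1-hour change shows the acute response to dose 1. At weeks 8 and 16 the same rule compares the 1-hour reading with one taken 8 or 16 weeks before, although a pre-dose reading from the same day exists. The tabulated change then answers how far the patient is from the pre-treatment value. It does not answer what happened in the hour after this injection.

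The second question matters in this trial. Safety and tolerability is the primary objective. Section 1.6.1 says that the safety of repeated administration at 2-month intervals has still to be established, and section 1.6.2 says the same of the effects of the longer intervals. Section 1.4 reports immediate symptoms in dogs that were re-dosed after at least five days. ECGs are recorded before dosing (section 7.2.6), and PK is sampled at the first dose only. The 1-hour blood pressure, pulse and temperature are therefore the only physiological measurements with a stated time after doses 2 and 3.

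**Working it through.** The plan gives no figure for this point, so there is nothing to reproduce. The documents also give no variability for vital signs. Every SD, correlation and effect size below is an assumption.

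**Decomposition.** Let P0 be the day-0 pre-dose value, Pk the pre-dose value at week 8 or 16, and Ak the 1-hour value at that visit.

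Ak − P0 = (Ak − Pk) + (Pk − P0) = acute change + drift.

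The sign of the left side is wrong when drift is opposite to the acute change and larger. Example with invented systolic values: P0 = 140, Pk = 122, Ak = 134. The stated rule gives 134 − 140 = −6 mmHg. The change after the injection is 134 − 122 = +12, and the drift is 122 − 140 = −18.

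**Spread of the change.** Assume a visit-to-visit SD within a patient of sv = 8 mmHg and a within-visit SD of sw = 5 mmHg.
- From day 0: √(2(sv² + sw²)) = √(2 × 89) = √178 = 13.3 mmHg.
- From the same-visit pre-dose value: √(2sw²) = √50 = 7.1 mmHg.
- Variance ratio: 178/50 = 3.6. It is 104/32 = 3.3 for SD pair 6/4 and 272/72 = 3.8 for 10/6.
- SE of an arm mean with n = 8: 13.3/√8 = 4.7 against 7.1/√8 = 2.5 mmHg.

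**Wrong sign for an assumed true acute change of −10 mmHg, no mean drift.**
- One patient: 1 − Φ(10/13.3) = 23%, against 1 − Φ(10/7.1) = 8%.
- Arm mean, n = 8: 1 − Φ(10/4.7) is about 2% from day 0, and negligible from the same visit (10/2.5 = 4 SE).

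**Wrong sign of a within-arm mean when there is mean drift (day-0 reference).**
- Drift +5 mmHg: 1 − Φ((10 − 5)/4.7), about 14%.
- Drift +12 mmHg: Φ((12 − 10)/4.7), about 66%.

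**Second model as a check.** Assume a total SD of 10–15 mmHg, between-visit correlation 0.5–0.7 and within-visit correlation 0.8–0.9, with SD of change = SD × √(2(1 − r)).
- SD of change: 7.7–15.0 mmHg from day 0, against 4.5–9.5 from the same visit.
- Wrong sign for −10 mmHg in one patient, no mean drift: 10–25% against 1–15%.
- Wrong sign of an arm mean from day 0: 0–3% with no mean drift, 3–17% with +5, and 65–77% with +12.
- Active minus placebo (8 against 8, common drift cancelled): SE 3.9–7.5 against 2.2–4.7 mmHg; wrong sign 0.5–9% against 0–1.8%.

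**What the planned tables still allow.** The pre-dose and 1-hour values share the same P0. With complete pairs, and if both time points are tabulated, mean(Ak − P0) − mean(Pk − P0) = mean(Ak − Pk). The mean acute change can be recovered by subtraction. Its SD, median, minimum and maximum cannot.

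**The case against.** The strongest reply is that section 6.2 defines baseline and does not forbid other contrasts. Section 10.3 leaves analysis detail to a statistical analysis plan, and a table of pre-dose to 1-hour change is an ordinary derivation there. This limits the point but does not remove it. The protocol is not silent: it states a comparator for treatment-period measurements, the synopsis plans changes from it, and no other reference is named.

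A reader might infer that acute reactions to doses 2 and 3 would be hidden. The documents do not support that. Both same-visit readings are collected, individual and summary values are presented, and a listing for the example above would show 122 followed by 134. Patients stay in hospital for 24 hours after each dose, with an adverse event review at 24 hours, so a clinically apparent reaction is recorded whatever the vital-sign reference.

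A reader might also infer that drift biases the safety comparison. Mean drift common to the arms cancels against placebo, which is given in the same volume and manner. Chance imbalance with 8 per arm, the extra variance and any drift caused by treatment remain. Section 10.4 has the DSMB evaluate blinded data, where a placebo contrast may not be available. Safety is summarised without formal statistics, so the larger variance affects no planned test.

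Finally, the day-0 baseline is not in itself wrong. It is a valid measure of total change from before treatment.

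**Conclusion.** The point holds as a limited improvement to the analysis. As the rule stands, the planned change from baseline for the 1-hour blood pressure, pulse rate and temperature at weeks 8 and 16 combines acute change with drift. The planned change summaries therefore do not show the distribution of within-patient acute change after re-dosing. Three variables at two visits are affected. Day-0 readings and visits without dosing are not.

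Under the assumed SDs of 8 and 5 mmHg, the SD of change is 13.3 against 7.1 mmHg, and a true fall of 10 mmHg takes the wrong sign in 23% against 8% of patients. For an arm mean without mean drift, the wrong-sign risk is only about 2%; it becomes substantial only if mean drift is opposite to the acute change and of similar or larger size. It would go too far to conclude that the reported direction will generally be wrong, or that safety information is lost. The decomposition follows from the protocol text alone; the magnitudes rest wholly on assumptions.

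**What to change.** In section 6.2 and in the safety analysis (synopsis and section 10.3.2), keep the day-0 baseline for total change and add wording such as: for the 1-hour blood pressure, pulse rate and body temperature on each dosing day, the change from the pre-dose value of the same visit is also calculated, and is summarised by dose number and treatment group, including placebo.

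The cost is one sentence and one extra table. All values needed are already collected, and no visit, measurement or clinical rule changes.

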## Follow-up period (week 24-week 48)

During the follow-up period, patients will return to the hospital for ambulatory visits twice to undergo the assessments according to the schedule of assessments, section 6.5.

The last available values measured prior to first study drug administration will be considered baseline measurements against which measurements during the follow-up period will be compared.

## Early Termination

In case of any early termination from the study treatment, the patient will be asked to continue scheduled evaluations, complete an end-of-study evaluation, and be given appropriate care under medical supervision until the symptoms of any adverse event resolve, or the patient’s condition becomes stable. In case of complete withdrawal from the study, all reasonable efforts should be undertaken to obtain the assessments as specified for the week 24 visit in the schedule of assessments.

## Schedule of assessments

Table 6‑1 Schedule of assessments

| **Assessment** | **Week -4 to -1 (screening)** | **Day 0** | **Week 1**  **± 1 d** | **Week 2**  **±1 d** | **Week 4**  **± 3 d** | **Week 8**  **± 3 d** | **Week 12**  **± 3 d** | **Week 16**  **± 3 d** | **Week 20**  **± 3 d** | **Week 24 or EoT**  **± 3 d** | **Week 36**  **± 3 d** | **Week 48**  **± 3 d** |
| --- | --- | --- | --- | --- | --- | --- | --- | --- | --- | --- | --- | --- |
| Written consent | x |  |  |  |  |  |  |  |  |  |  |  |
| Inclusion/Exclusion criteria | x |  |  |  |  |  |  |  |  |  |  |  |
| Demographic data | x |  |  |  |  |  |  |  |  |  |  |  |
| Medical History | x |  |  |  |  |  |  |  |  |  |  |  |
| Previous medication | x |  |  |  |  |  |  |  |  |  |  |  |
| Study drug administration^4^ |  | x |  |  |  | x |  | x |  |  |  |  |
| MRI | x |  |  | x | x | x^3^ | x | x^3^ | x | x | x | x |
| EDSS | x | x |  |  |  | x |  | x |  | x | x | x |
| MSIS-29 |  | x |  |  |  | x |  | x |  | x | x | x |
| Neurological evaluation/clinical relapse | x | x | x | x | x | x | x | x | x | x | x | x |
| Blood sample for effect parameters (T-cell response | x | x |  |  | x | x | x | x | x | x | x | x |
| Anti-CRYAB/DC-TAB antibodies | x | x |  |  | x | x | x | x | x | x | x | x |
| Safety Laboratory Tests (Haematology, Biochemistry, Urinalysis) ^6^ | x | x | x |  | x | x |  | x |  | x | x | x |
| Urine Pregnancy Test | x |  |  |  |  | x |  | x |  | x |  |  |
| PK sampling | x^8^ | X^1^ |  |  |  |  |  |  |  |  |  |  |
| Physical examination | x | x | x | x^2^ | x^2^ | x | x^2^ | x | x^2^ | x | x^2^ | x |
| Vital Signs ^7^ | x | x |  |  |  | x |  | x |  | x |  | x |
| Body temperature^7^ | x | x |  |  |  | x |  | x |  |  |  |  |
| 12-Lead ECG | x | x |  |  |  | x |  | x |  | x |  | x |
| Adverse events |  | X^5^ | x | x | x | x^5^ | x | x^5^ | x | x | x | x |
| Concomitant medication |  | x | x | x | x | x | x | x | x | x | x | x |

^1^ Samples (relative to study drug administration) at pre-dose, t=10 minutes, t=20 minutes, t=30 minutes, t=1 hour, t=2 hours, t=4 hours, t=8 hours, t=16 hours, t=24 hours;

^2^ Brief physical examination (symptom guided)

^3^ MRI can be made on dosing days after study drug administration

^4^ On study drug administration visits need patient hospitalization for 24h after dosing.

^5^ Repeated adverse event review is needed 24 hours after each dosing

^6^ See the full list of the laboratory parameters in section 7.2.1.

^7^ On dosing days blood pressure, pulse rate and temperature will be measured before and 1 hour after dosing; respiration rate only pre-dose.

All assessments are to be done prior to study drug administration unless otherwise stated.

^8^ Ten patients only; one sample collected to further investigate the stability of blood samples

## Compliance with the protocol

Any deviation from the protocol must be explained. Any patient who is entered into the study but is found not to meet the protocol entry criteria will be considered for withdrawal as a protocol violator after consultation with the sponsor.

# Methodology of assessments

## Baseline variables

### Demographics

At screening, the following demographic data will be collected: gender, date of birth, race, body weight, height and smoking habit.

### Medical history

Complete medical history will be reviewed at screening. This will include evaluation for past and present cardiovascular, respiratory, gastrointestinal, renal, hepatic, neurological, endocrine, lymphatic, hematological, immunological, dermatological, psychiatric, genitourinary, and surgical history and rhinoconjunctivitis history and any other diseases or disorders.

### Previous Medication

The investigator should record the use of all medications used within 3 months prior to entry in the study, both prescribed and over-the-counter, on the CRF. This includes drugs used on a chronic and as-needed basis. The following will be recorded on the CRF: Drug name (trade name), total daily dose, route, start and end date and time, whether ongoing and indication.

All previous medication will be coded using the World Health Organization’s Drug Dictionary (WHO-DD).

### McDonald criteria

Diagnosis at baseline is established using the Revised McDonald criteria (Polman et al. 2011).

| **Clinical Presentation** | **Additional Data Needed** |
| --- | --- |
| - 2 or more attacks (relapses) - 2 or more objective clinical lesions | None; clinical evidence will suffice  (additional evidence desirable but must be consistent with MS) |
| - 2 or more attacks - 1 objective clinical lesion | Dissemination in space, demonstrated by:   - MRI - or a positive CSF and 2 or more MRI lesions consistent with MS - or further clinical attack involving different site |
| - 1 attack - 2 or more objective clinical lesions | Dissemination in time, demonstrated by:   - MRI - or second clinical attack |
| - 1 attack - 1 objective clinical lesion   (monosymptomatic presentation) | Dissemination in space by demonstrated by:   - MRI - or positive CSF and 2 or more MRI lesions consistent with MS   ***and***  Dissemination in time demonstrated by:   - MRI - or second clinical attack |
| Insidious neurological progression  suggestive of MS  (primary progressive MS) | Positive CSF  ***and***  Dissemination in space demonstrated by:   - MRI evidence of 9 or more T2 brain lesions - or 2 or more spinal cord lesions - or 4-8 brain and 1 spinal cord lesion - or positive VEP with 4-8 MRI lesions - or positive VEP with <4 brain lesions plus 1 spinal cord lesion   ***and***  Dissemination in time demonstrated by:   - MRI - or continued progression for 1 year |

## Safety variables

The safety and tolerability of the investigational products will be evaluated by monitoring the patient’s AE profile and local tolerability throughout the study, the assessment of routine safety laboratory tests, physical examination, vital signs and 12-lead ECG.

### Safety laboratory Parameters

Blood (approximately 8 ml of blood per visit) and urine specimens for safety laboratory testing will be taken according to the schedule of assessments (see section 6.5). The laboratory tests will be coordinated / performed by the local laboratory.

Hematology will include hemoglobin (Hb), hematocrit (Hct), red blood cell count (RBC), platelet count, white blood cell count (WBC) and absolute differential count (neutrophils, basophils, eosinophils, monocytes, and lymphocytes).

Biochemistry will include alanine aminotransferase (ALT), aspartate aminotransferase (AST), alkaline phosphatase (ALP), total bilirubin, gamma glutamyl transferase (GGT), lactate dehydrogenase (LDH), total protein, albumin, urea, creatinine, sodium, potassium and chloride. In addition, eGRF will be calculated using the MDRD formula (GFR = 186.3 x SerumCr^-1.154^ * age^-0.203^ * 1.212 (if patient is black) * 0.742 (if female); an MDRD calculator can be found on MDcalc.com).

Urinalysis (semi-quantitative analysis per dipstick) will include protein, glucose, nitrite, pH, ketones, and blood. If protein, nitrite or blood is abnormal in the urine sample, microscopy will be done.

### Urine pregnancy tests

Urine pregnancy tests will be performed on all females according to the schedule of assessments (see section 6.5). Pregnancy tests will be performed at the study centre. In the event that the patient is withdrawn, a urine pregnancy test will be performed at the last visit.

### Physical Examination

Physical examinations will be performed at all visits. The examinations will include the following: general appearance, HEENT (head, ears, eyes, nose and throat), skin, cardiovascular system, respiratory system, gastrointestinal system, nervous system and other. At the visits of week 2, 4, 12, 20 and 36 a brief, symptom guided physical examination will be performed, if applicable.

### Vital Signs

Blood pressure (systolic (SBP) and diastolic (DBP)), pulse rate and respiration rate after 10 minutes supine rest will be recorded on each dosing days and at weeks 36 and 48. On dosing days, evaluations will be done pre-dose and, in addition, blood pressure and pulse rate will be assessed at 1 hour after dosing. Automatic or manual devices may be used. All devices must have been calibrated in the previous 12 months. Calibration certificates must be available on request.

### Body temperature

Body temperature will be measured at each dosing visit. On dosing days, body temperature will be measured pre-dose and at 1 hour after dosing.

